# The impact of physical training on length of hospital stay and physical function in patients hospitalized with community-acquired pneumonia: protocol for a randomized controlled trial

**DOI:** 10.1186/s13063-021-05503-2

**Published:** 2021-08-28

**Keywords:** Community-acquired pneumonia, Physical training, Length of hospital stay, Lean mass, Functional ability

## Abstract

**Background:**

Community-acquired pneumonia (CAP) is a leading cause of hospitalization worldwide. Bed rest with low levels of physical activity is common during periods of hospitalization and leads to functional decline as well as increased risk of complications. The aim of this study is to assess the effect of supervised physical training during hospitalization with CAP compared with standard usual care for CAP on length of hospital stay, risk of readmission, mortality risk, physical capacity, muscle and fat mass, muscle strength, metabolic function, systemic inflammation, health-related quality of life, and physical activity level.

**Methods:**

This study is a randomized controlled trial with three parallel experimental arms. Based on a sample size calculation, a total of 210 patients admitted with CAP at Nordsjællands Hospital, Hillerød, Denmark, will be recruited. Patients will be randomly allocated (1:1:1) to either (1) standard usual care, (2) standard usual care combined with in-bed cycling, or (3) standard usual care combined with exercises from a booklet. The primary outcome is differences in length of hospital stay between groups, with secondary outcomes being differences between groups in time to (1) 90-day readmission and (2) 180-day mortality. Further secondary outcomes are differences in changes from baseline between groups in (3) lean mass, (4) fat mass, (5) fat-free mass, (6) physical capacity, (7) health-related quality of life, (8) systemic inflammation, and (9) physical activity level after discharge. Data on length of hospital stay, readmission, and mortality will be collected from patient files, while total lean, fat, and fat-free mass will be quantitated by dual-energy x-ray absorptiometry and bioelectrical impedance analysis. Physical function will be assessed using grip strength, 30-s chair stand tests, and Barthel Index-100. Health-related quality of life will be assessed with the EQ-5D-5L questionnaire. Systemic inflammation will be assessed in blood samples, while accelerometers are used for measuring physical activity.

**Discussion:**

If a simple physical training program appears to diminish the impact of critical illness and hospitalization on clinical outcome, mobility, and health-related quality of life, it may lead to novel therapeutic approaches in the treatment of patients hospitalized with CAP.

**Trial registration:**

ClinicalTrials.gov NCT04094636. Registered on 1 April 2019

**Supplementary Information:**

The online version contains supplementary material available at 10.1186/s13063-021-05503-2.

## Background

Community-acquired pneumonia (CAP) is a leading cause of hospitalization and death from infectious diseases worldwide [1], with an overall mortality of 14% in patients hospitalized with CAP [2]. The incidence of patients hospitalized with pneumonia has been increasing in Denmark through the past 2 decades from 288 to 809 per 100.000 person-years and is predicted to continue rising due to the aging of the population [3, 4]. One out of five patients are readmitted within 30 days, making readmissions a significant burden both for the patient and the health care system [5]. Hospitalization is associated with bed rest which can result in prolonged physical inactivity and immobilization. In fact, patients hospitalized with CAP spent over 90% of their waking hours being physically inactive, i.e., either laying or sitting down, with only 926 steps per day during admission [6, 7]. Moderate to severe frailty is a predictor of lower daily step count. It has been reported that frail patients take 59% less steps per day during admission compared to robust patients [6], which can exacerbate physical deterioration several weeks after discharge [8]. Frail patients with frequent readmissions may be prone to a more rapid decline in functional ability and associated deteriorations in health-related quality of life [9], which may cause a *viscous cycle* of physical inactivity with negative effect on the prognosis [10–12] (Fig. 1).

**Fig. 1 Fig1:**
[figure not shown]
Breaking the vicious cycle of hospitalization, disability, and poor prognosis through physical training. Dark colors, e.g., dark gray, dark blue, and dark green, indicate processes which takes place in hospital during hospitalization. Lighter colors, e.g., light gray, light blue, and light green, indicate time periods, which takes place at home after discharge

Previous studies have shown that only 10–14 days of bed rest leads to a substantial loss of lower extremity muscle mass and muscle strength, increase in visceral fat, and impairments in insulin sensitivity in healthy individuals [13–16]. Moreover, these bed rest-related changes were associated with a reduction in physical activity level during the week following bed rest [13]. However, early mobilization of patients with CAP within the first 24 h of hospitalization has been shown to decrease length of hospital stay by 1.1 to 2.1 days without increasing the risk of adverse events [17–19]. In addition, for every increase in the daily step count above 500 steps, length of hospital stay was reduced by 11% among patients with CAP [6]. Moreover, we have previously shown that initiating supervised early pulmonary rehabilitation of patients with acute exacerbation of chronic obstructive pulmonary disease (COPD) during hospitalization is superior to standard usual care in terms of improving prognosis (reduces the risk of COPD-related hospital readmissions), health-related quality of life, and walking distance [20].

Even though international guidelines for the management of patients hospitalized with CAP recommend early mobilization as part of standard of care for CAP [21], the physical activity level among patients hospitalized with CAP remains low. Despite the emerging evidence that physical activity during hospitalization for respiratory conditions is beneficial in terms of improving functional outcomes, it is not consistently prioritized in clinical practice. Therefore, interventions that increases physical activity and interrupt sedentary time during hospitalization are crucial (Fig. 1).

## Methods/design

### Study design and study setting

The study is a single-center, randomized, superiority, open-label, controlled trial with three parallel experimental arms, nested in a prospective cohort study. Over a 3-year period, all patients hospitalized with suspicion of lower respiratory tract infection at the Emergency Department at Nordsjællands Hospital, Hillerød, Denmark, will be screened for eligibility. Based on a sample size calculation, a total of 210 patients hospitalized with CAP are randomized in a ratio of 1:1:1 to standard usual care or standard usual care combined with daily supervised physical training consisting of either in-bed cycling or booklet exercises as depicted in Fig. 2. The enrolment period began on 1 April 2019 and is estimated to be completed by 1 March 2022. All baseline and discharge tests are carried out at the Department of Pulmonary and Infectious Diseases, Nordsjællands Hospital, Hillerød, Denmark. The follow-up tests are carried out at Department of Pulmonary and Infectious Diseases, Nordsjællands Hospital, Hillerød, Denmark or as home visits.

**Fig. 2 Fig2:**
[figure not shown]
Flow of patients though the study. Any reasons for discontinuation or exclusion from analysis are reported

### Study hypotheses and aims

We hypothesize that standard usual care combined with daily supervised in-bed cycling or standard usual care combined with booklet exercises is superior to standard usual care alone in reducing length of hospital stay, reducing the risk of 90-day readmission, and 180-day mortality, counteracting loss of muscle mass, muscle strength, functional ability, low/reduced health-related quality of life, increase in fat mass, reducing systemic inflammation, and increasing the physical activity level after discharge.

The primary aim of the study is to determine if supervised in-bed cycling or supervised booklet exercises during hospitalization with CAP reduces length of hospital stay. Secondary aims are to determine if supervised in-bed cycling or supervised booklet exercises during hospitalization with CAP improves prognosis (e.g., reduces the risk of readmission and mortality) and minimizes/counteracts hospital-related changes in body composition, muscle strength, functional ability, health-related quality of life, systemic inflammation, and physical activity level after discharge. Additional aims are to investigate if supervised in-bed cycling or supervised booklet exercises during hospitalization with CAP improves glucose metabolism, diabetes and health status, and frailty.

## Participant selection

### Eligibility

Patients are screened through patient files for eligibility within the first 24 h after hospital admission by a physician or study nurse affiliated with the study. Patients are eligible if they are age ≥18 years and hospitalized with CAP. The definition of pneumonia is presence of a new infiltrate on chest X-ray/CT and minimum one of the following symptoms: temperature < 35 °C or ≥38 °C, cough, pleuritic chest pain, dyspnea, or focal chest signs on auscultation. To be enrolled, patients must have an expected length of hospitalization of ≥72 h and the ability to move their legs. Patients will be excluded if they are immunosuppressed (cancer chemotherapy ≤28 days, neutropenia ≤1000 cells/μL, ≥20 mg prednisolone-equivalent/day >14 days or other immunosuppressive drugs, HIV infection, former transplant) or have been hospitalized within ≤14 days (Table 1).

**Table 1 Tab1:** Eligibility of study participants

Inclusion criteria	Exclusion criteria
1. Age ≥ 18 years 2. Expected length of hospitalization ≥72 h 3. New infiltrate on chest X-ray/CT 4. One or more of the following symptoms: a. Temperature <35 °C or ≥38 °C b. Cough c. Dyspnea d. Pleuritic chest pain e. Focal chest signs on auscultation	1. Patients unable to give written consent 2. Hospitalization within ≤ 4 days 3. Inability to move their legs 4. Immunosuppression a. Treatment with ≥20 mg corticosteroids >2 weeks b. Chemotherapy c. Neutropenia with neutrophils <0.5 × 10^9^/L d. Ongoing treatment with biological drugs e. Chronic HIV-infection with CD4 cell count <350 mio/L f. Immunosuppression after organ transplantation 5. Terminal ill patients where active treatment is stopped within the first 48 h of admission

## Interventions

The intervention is a combination of standard usual care for CAP and daily supervised physical training tested with 2 different training modalities: exercise booklet and in-bed cycling. The resulting intervention and standard usual care group are depicted in Fig. 2. While mobilization defined as movement out of bed with change from horizontal to upright position for at least 20 min per day is imbedded in the standardized treatment for patients hospitalized with CAP [21], it is often neglected and only sporadically addressed. Own data shows that only 21% of the patients have notes on mobilization in their patient file. The lack of systematic mobilization is criticizable as the impact on patient-related outcomes is well-established [17, 22]. Barriers for mobilization often includes restricted/lack of time for mobilization, patient’s lack of motivation for mobilization, and problems with nurses not viewing mobilization as part of their core task [23]. In Denmark, hospitalized patients only receive physiotherapy if it is prescribed by the physician. The study will record from patient files if a patient receives respiratory physiotherapy, exercise training by a physiotherapist, mobilization, or rehabilitation plans.

### Exercise booklet

The exercise intervention with the exercise booklet is chosen as it is aims towards the sick hospitalized patient. The exercise booklet (Fig. 3) includes strengthening and walking exercises with varying degree of difficulty that can be easily done during hospitalization to ensure that all patients are challenged to be physically active, irrespectively of mobility (bedridden or ambulant). The functional exercises from the booklet are designed to challenge stability, strength, and endurance in order to train the patient’s ability to perform activities of everyday life after discharge. Patients allocated to the exercise booklet group will daily receive 30 min of supervised physical training after an exercise booklet (entitled “Syg men Sund og Aktiv” [“Sick but Healthy and Active” in English], The Centre for Physical Activity Research, Copenhagen, Denmark). Every exercise session is supervised and instruction by an exercise physiologist or physiotherapist student. The selection of exercises is left to the exercise instructor training the patient. The patients will perform 3 times 10 repetitions of each selected exercise from the strengthening programs for either bedridden (Fig. 3a) or ambulant (Fig. 3b) patients. The strengthening exercises will be combined with exercises from the walking program (Fig. 3c) giving each exercise session a total of 30 min.

**Fig. 3 Fig3:**
[figure not shown]
Exercise programs from the exercise booklet. The exercises are designed for bedridden and ambulant patients. The exercises are divided into 3 programs; **A**, **B**, and **C**, respectively. Programs **A** and **B** include strengthening exercises divided into varying degrees of difficulty (e.g., very easy or easy) for both bedridden (**A**) and ambulant patients (**B**). Program C includes different walking programs

### In-bed cycling

The exercise intervention with in-bed cycling is chosen as it has been shown to be a safe and feasible method to mobilize patients at the intensive care unit (ICU) [24]. For patients who are unable to get out of bed, in-bed cycling could be an alternative and effective method to mobilize patients. The in-bed cycling may further improve endurance and muscle performance of the lower limbs allowing the patient to be able to get out of bed and eventually walking around. As the patient’s physical capacity improves resistance, pace, and exercise time increases in order to induce a continuous training stimulus. Patients allocated to the in-bed cycling groups will daily receive a total of 30 min supervised physical training under the guidance and instruction of an exercise physiologist or physiotherapist student. Patients will exercise for 25 min on the bed bike (Lemco Rehab & Fysio, Helsingør, Denmark) at an individual power, which is set to be tolerated for 25 min and perform exercises from the exercise booklet for 5 min. Again, the selection of exercises is left to the exercise instructor training the patient. Exercises from the exercise booklet is included in the exercise program for the in-bed cycling group in order to introduce and familiarize the patients with the exercises that we encourage them to performed after discharge.

## Training diary and exercise booklet

Upon discharge, patients from the two exercise groups (exercise booklet and in-bed cycling group) will receive a copy of the exercise booklet, a training diary, and encouragement to remain physically active. Patients will be instructed to note information about their physical training at home (e.g., modality, intensity, duration) in the training diary the 1st month after discharge and return the training diary to the study team at the 1-month follow-up visit.

## Follow-up

The follow-up visits take place at the Department of Pulmonary and Infectious Diseases, Nordsjællands Hospital, Hillerød or as home visits, 1 and 3 months after discharge. During the follow-up visits, investigations performed during hospitalization will be repeated (Fig. 4). A phone interview assessing health-related quality of life, physical activity level, functional ability, and frailty will be performed at 6 months after discharge. Data concerning readmission and mortality will be collected from electronic capture from patient files up to 6 months after discharge, while development of type 2 diabetes will be collected up to 2 years after discharge.

**Fig. 4 Fig4:**
[figure not shown]
SPIRIT standard protocol items with time schedule of enrolment, interventions and assessments. *BIA* bioelectrical impedance analysis, *DXA* dual-energy X-ray absorptiometry, *ECG* electrocardiogram, *EQ-5D-5L* health-related quality of life, *HbA1c* hemoglobin A1c, *IPAQ* International Physical Activity Questionnaire, *OGTT* oral glucose tolerance test. Asterisk indicates standard usual care. Superscript digit 1 indicates the following: After radiological diagnose of pulmonary infiltrate on chest X-ray/CT in combination with at least one symptom of lower respiratory tract infection at admission, eligibility will be assessed, and potential participants will be approached. Superscript digit 2 indicates the following: The physical training is a supervised exercise program with one session per day. Superscript digit 3 indicates the following: Basic blood samples will be drawn daily as part of routine tests during hospitalization and analyzed for hematologic, renal, endocrine, cardiac, and hepatologic markers. Blood samples stored in the biobank will be analyzed for markers of inflammation. Superscript digit 4 indicates the following: Readmission up to 3 months after discharge. Superscript digit 5 indicates the following: mortality during admission and up to 6 months after discharge. The table is adapted from the SPIRIT recommendations [25]

## Outcomes and timing of assessments

The attending physician will evaluate whether the patient is ready for discharge. Readiness for discharge is based on the modified Halm’s criteria for clinical stability in CAP [26]. Once the criteria are met, the different measurements scheduled for discharge will be performed. The different outcome variables and timing of assessments are listed in Table 2.

**Table 2 Tab2:** Outcome

Outcome domain	Specific measurement	Specific metric				Methods of aggregation			Time point
		Value at a time point	Change from baseline	End value	Time to event	Mean	Percent/proportion	Absolute number	
Length of hospital stay	Discharge date–admission date			x		x			Discharge
Readmission	Readmission date–discharge date				x		x	x	3 months
Mortality	Mortality date–discharge date				x		x	x	6 months
Total lean mass	DXA scan		x			x			Discharge
Total fat mass	DXA scan		x			x			Discharge
Total fat-free mass	BIA scan		x			x			Discharge
Leg lean mass	DXA scan		x			x			Discharge
Trunk fat mass	DXA scan		x			x			Discharge
Health-related quality of life	EQ-5D-5L		x			x			Discharge
Activities of daily living	Barthel Index-100		x			x			Discharge
Muscle strength	Hand grip strength		x			x			Discharge
Muscle endurance	30-s chair stand test		x			x			Discharge
Systemic inflammation	Plasma samples		x			x			Discharge
Physical activity	AX3 accelerometers		x			x			After discharge
Glucose metabolism	Oral glucose tolerance test		x			x			3 months
Diabetes status	HbA1c	x					x	x	3 months
Prior physical activity level	IPAQ questionnaire	x					x	x	3 months
Frailty	Frail scale questionnaire	x					x	x	3 months

*BIA* bioelectrical impedance analysis, *DXA* dual-energy x-ray absorptiometry, *EQ-5D-5L* health-related quality of life, *HbA1c* hemoglobin 1Ac, *IPQA* International Physical Activity Questionnaire

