### Secondary outcomes

The secondary outcomes are readmission and mortality measured as time to event within 3 and 6 months from discharge, with comparisons between the groups. Total lean mass, total fat mass, total fat-free mass, leg lean mass, and trunk fat mass measured as mean changes from admission to discharge and from discharge to 3 months after discharge, with comparisons between groups. Health-related quality of life and activities of daily living measured as mean change from admission to discharge and from discharge to 3 months after discharge, with comparisons between groups. Muscle strength and endurance measured as mean change from admission to discharge and from discharge to 3 months after discharge, with comparisons between groups. Systemic inflammation measured as mean change from admission to discharge and from discharge to 3 months after discharge, with comparisons between groups. Accelerometer-based physical activity level measured at admission as mean change from admission to the week after discharge, with comparisons between groups.

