### Blood samples

Venous blood samples are collected daily in the morning (between 7 and 9 am) as part of routine tests during admission and will be analyzed the same day according to local guidelines from the Department of Clinical Biochemistry, Denmark, and thus are not affected by the study. This provides access to basic blood work such as complete blood count (white blood cell differential, red blood cell count, platelets), C-reactive protein, coagulation factors, procalcitonine, kidney function, liver function, and electrolytes. In addition to basic blood work diabetes biomarkers such as HbA1c, fasting glucose, fasting insulin, and fasting c-peptide, lipid status (total cholesterol, high-density lipoprotein (HDL) cholesterol, low-density lipoprotein (LDL) cholesterol, and triglycerides) is measured. Besides routine blood samples during admission, additional venous blood samples (plasma, serum, and whole blood) will be collected from all included patients. Plasma and serum samples will be centrifuged at 3,000 × *g* for 15 min at 4 °C and stored together with whole blood in a biobank at − 80 °C until analysis. At the day of inclusion (day 0), plasma, serum, and whole blood samples will be obtained. At days 1–5 and follow-up visits at 1 and 3 months after discharge, plasma and serum samples will be obtained. Biobank samples will be analyzed for inflammatory cytokines and chemokines (e.g., tumor necrosis factor alpha (TNF-α), interleukin (IL)-1β, IL-6, IL-8, IL-10, and IL-18).

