## Statistical power and sample size calculations

The sample size calculation is performed using www.powerandsamplesize.com and is based on the primary outcome, length of hospital stay. The expected reduction in length of hospital stay is based on data from a previous study showing a reduction (3.9 days vs. 6.0 days) for patients hospitalized with CAP randomized to either early mobilization or standard usual care [18]. The number of patients with CAP is based on a 2-day difference in length of hospital stay between CAP patients receiving standard usual care compared to standard usual care combined with daily physical training. The standard deviation for this calculation is 3.5 days, as previous observed [18]. Assuming an estimated drop-out rate of 15%, inclusion of 210 patients (70 patients in each group) will provide a power of > 0.8 at a two-sided significance level of 0.025, adjusted for multiple comparisons (0.05/2).

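### The admission-to-discharge changes are timed by an event that training is expected to bring forward by about 2 days, so alone they cannot separate a shorter stay from an effect on inflammation, muscle or function

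*Protocol article*

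**What the plan says.** All places are in the protocol article.

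- **Trigger.** Under *Outcomes and timing of assessments*: "Readiness for discharge is based on the modified Halm’s criteria for clinical stability in CAP". The next sentence reads: "Once the criteria are met, the different measurements scheduled for discharge will be performed".
- **Outcomes.** Table 2 gives discharge as the time point, as change from baseline, for ten secondary outcomes: five body-composition measures, EQ-5D-5L, Barthel Index-100, grip strength, chair stand and systemic inflammation. *Secondary outcomes* defines the body-composition measures as "measured as mean changes from admission to discharge and from discharge to 3 months after discharge, with comparisons between groups", and uses the same two windows for the other five.
- **Expected shift.** *Statistical power and sample size calculations* plans for a "2-day difference in length of hospital stay", based on an earlier trial "showing a reduction (3.9 days vs. 6.0 days) for patients hospitalized with CAP".
- **Analysis.** *Pre-planned analysis* compares changes from baseline in linear mixed models with a treatment-by-time interaction. It states no term for elapsed days.
- **Other visits.** A 1-month visit repeats these measurements, but neither Table 2 nor *Secondary outcomes* uses it to define any of the ten outcomes.
- **Measurement schedules.** *Anthropometry and body composition* lists DXA at day 0 or 1, day 5, and 1 and 3 months, with no discharge scan. *Blood samples* lists biobank samples on day 0 and then: "At days 1–5 and follow-up visits at 1 and 3 months after discharge, plasma and serum samples will be obtained". It lists no discharge sample. *Measurement of outcome variables* says that the baseline tests are repeated at discharge.

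**The concern.** The discharge test follows an event after randomisation that the treatment is meant to move. If the primary hypothesis is true, trained patients are tested about 2 days earlier in their illness. All patients are also tested on reaching a common stability threshold. Either feature can create or hide a difference between arms.

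- **A quantity that drifts with days in bed, such as lean mass.** Fewer counted days look like preserved muscle, even if the loss per day is the same or continues at home.
- **A quantity that recovers with time, such as an inflammatory marker or chair stand.** Earlier testing leaves less time to recover, and the common threshold pulls the arms together. Effective training could show no difference or a worse value.

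At stake is what the trial can conclude. Its secondary aims include limiting hospital-related changes in body composition, strength, function and inflammation. A reader of the results will want to know whether any difference goes beyond the shorter stay.

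**Working it through.** **Inputs from the article:** stays of 3.9 and 6.0 days, planned difference 2 days, SD 3.5 days, two-sided alpha 0.025 per comparison, power above 0.8, drop-out 15%, 70 per arm.

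**1. The plan's own figure.** n per arm = 2 × (3.5/2)² × (z₀.₉₈₇₅ + z₀.₈₀)² = 58.2, rounded up to 59. 59/0.85 = 69.4, rounded up to 70. 70 × 3 = 210. The sample size reproduces.

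**2. Gap in timing between arms.**
- Discharge test: 6.0 − 3.9 = 2.1 days; 2.1/6.0 = 35%.
- One-month visit (30 days after discharge): 36.0 against 33.9 days from admission; 2.1/36 = 6%.

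**3. What a 2-day gap can do with no per-day training effect.** If an outcome drifts by c per hospital day in every arm, the admission-to-discharge changes differ by 2c. The article gives no c, so the range below is assumed. The simulation used 59 per arm, gamma stays with means 6 and 4 and SD 3.5, a two-sided t-test at 0.05 and 20,000 runs. SD here is the residual SD of the change.

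| Assumed drift, SD per day | Difference between arms, SD | Chance of p < 0.05 |
|---|---|---|
| 0 | 0 | 5% |
| 0.05 | 0.10 | 9% |
| 0.10 | 0.20 | 18% |
| 0.20 | 0.40 | 42% |
| 0.30 | 0.60 | 61% |

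**4. A decaying marker, with assumed half-lives h.** The ratio of discharge levels is 2^(2.1/h). The fall from baseline is 1 − 2^(−t/h).

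| h, days | Level ratio, day 3.9 to day 6.0 | Fall by day 3.9 | Fall by day 6.0 |
|---|---|---|---|
| 1 | 4.3 | 93% | 98% |
| 2 | 2.1 | 74% | 88% |
| 3 | 1.6 | 59% | 75% |

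The ratio matters on a log scale. On the raw change scale the gap is 5 to 16 percentage points of baseline. The article allows log transformation of right-skewed outcomes but does not fix the scale for inflammation.

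**5. Can a fixed in-hospital day replace discharge?** Share still in hospital, with gamma or lognormal stays of mean 3.9 or 6.0 and SD 3.5, ignoring the entry criterion of an expected stay of at least 72 h:

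| Day | Training | Usual care |
|---|---|---|
| 2 | 64–69% | 92–96% |
| 3 | 48–49% | 81–84% |
| 5 | 24–28% | 53–54% |

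The entry criterion should raise the early figures. Day 5 is clearly selective, and day 2 is less exposed than day 3.

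**The case against.** The strongest reply is that change over the stay is what the protocol asks about. *Study hypotheses and aims* speaks of hospital-related changes, and a shorter stay is part of the proposed mechanism. That stands: the contrast is a legitimate estimand and should stay.

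A reader might infer that the contrast is invalid, or that it is biased in a known direction against training. The document supports neither. The two mechanisms cannot both hold in full: an unchanged course sits poorly with stability reached 2 days sooner. They can also pull in different directions, and no net effect follows. The level ratios rest on assumed half-lives and do not describe raw change from baseline. For muscle, two days of drift may be small: the article's own background evidence is that "only 10–14 days of bed rest leads to a substantial loss of lower extremity muscle mass and muscle strength", which is far longer than the expected stay.

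It can also be said that the two defined windows add up to admission to 3 months, and that the coding of time may be settled in an analysis plan not shown. This is partly right. A nearly common-time contrast could be derived, but the article names none as an outcome, and discharge to 3 months starts from the shifted point.

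For the four DXA outcomes and inflammation, the measurement sections list no discharge assessment. There the point rests on Table 2, *Secondary outcomes* and *Measurement of outcome variables*.

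Finally, a 1-month contrast has weaknesses of its own. Only the exercise arms receive the booklet, diary and encouragement at discharge, and the pandemic has already caused missed visits. That is a reason to add this contrast beside the discharge contrast, not to replace it.

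**Conclusion.** The point holds as a limit on interpretation. The admission-to-discharge contrast mixes a shorter stay with any effect on the course of inflammation, muscle or function, because its timing depends on the primary outcome. Under the plan's own stays the timing gap is 2.1 of 6.0 days (35%). How far this distorts a given outcome depends on its daily course, which the article does not give; the drift and half-life tables are illustrations over assumed ranges. If training does not shorten the stay, the timing gap largely disappears.

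Alone, the contrast cannot support a claim that training reduced inflammation or preserved muscle or function apart from the shorter stay. A stronger reading, that it says nothing useful or should be reduced to a descriptive result, does not follow from the document. The primary outcome and the sample size of 210 are unaffected. The change is worth making, but the trial does not depend on it.

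**What to change.** 1. Keep the admission-to-discharge change, and report for each arm the day on which it was taken.
2. Add to Table 2 and *Secondary outcomes* the change from baseline to the scheduled 1-month visit for body composition, EQ-5D-5L, Barthel Index-100, grip strength and chair stand.
3. For systemic inflammation, add the change from day 0 to day 2, which is already a sampling day. Prefer day 2 to day 3 to limit selection by discharge, and report how many patients in each arm have the sample.
4. State that conclusions about inflammation, muscle or function will rest on agreement between the discharge contrast and the fixed-time contrasts.
5. Reconcile Table 2, *Secondary outcomes* and *Measurement of outcome variables* with *Blood samples* and *Anthropometry and body composition*, so that it is clear whether a discharge plasma sample and DXA scan exist.

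**Cost.** No new visit, sample or scan is needed for the added contrasts. Recruitment is under way, so this is an amendment to secondary outcomes. It should be dated, sent to the registry and committees as *Trial status* provides, and settled before any results by arm are seen. The 1-month contrast will have more missing visits and includes home exercise encouraged only in the training arms. The day-2 contrast reflects only a few sessions and still loses some early discharges.
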